### Allocation

Group allocation to IG and CG will be performed by minimization to obtain randomized groups with minimum group differences. Subjects rather than care facilities will be randomized to avoid confounding effects of the geographic location, and minimization will be done separately for each care facility based on the baseline criteria MMSE, sex, age, and baseline performance of modified 30-second chair-stand test. Minimization will be performed with the program MinimPy version 0.3 [75], which includes a random element. The first participant is allocated randomly to IG or CG. Subsequent participants are allocated to each group correspondingly to achieve the least imbalance between groups. Including a random element, participants will be allocated to the better fitting group with a probability of 70%. An allocation ratio of 2:1 is selected because of above-mentioned assumptions regarding dropouts. The input order of participants for allocation will be randomly defined by an assigned number for each participant given prior to minimization.

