## Methods

### Study Design

The study design has been primarily defined to address the primary aim of the study on the effectiveness of a 16-week MEP. For this reason, we will perform a multicenter randomized controlled trial with baseline and postassessments and an allocation ratio of 2:1 for intervention (IG) and control group (CG), respectively. Ethical approval has been obtained from the ethics commission of the Karlsruhe Institute of Technology. The study is retrospectively registered in the German National Register of Clinical Trials [DRKS00010538]. This study protocol considers guidelines and recommendations of the Standard Protocol Items: Recommendations for Interventional Trials (SPIRIT) [40,41] and Consolidated Standards of Reporting Trials (CONSORT) statements [42-44].

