### Intervention

The intervention is specifically developed for this study based on theoretical considerations, results of a pilot study [47], and a literature review [48]. The combination of motor and cognitive tasks used in the MEP aims to enhance the effectiveness of physical activity on cognition. This is theoretically supported by findings in healthy older adults showing that the combination of both yields larger effects on cognition than using each alone [49]. The pilot study (n=19) aimed to prove feasibility of the intervention and allowed first insights regarding the effectiveness. After a 10-week intervention, IG showed no significant changes in Alzheimer Disease Assessment Scale–Cognitive Subscale (ADAS-Cog, German version) [50] sum score but significant improvements in subscore orientation/praxis. In contrast, we found a significant decline in ADAS-Cog sum score of CG [47]. Moreover, IG showed significant improvements in get-up-and-go test whereas CG did not significantly improve (unpublished results). The literature review aimed at giving recommendations for designing interventions for IWD. Analyzed studies showed that a physical activity intervention for IWD should at least last 4 months with 2 to 3 sessions of 45 to 60 minutes per week. Moreover, interventions focusing on several motor skills (eg, endurance, strength, balance) seemed to be more effective than interventions with only 1 task [48]. Hence, the 10-week intervention of the pilot study has been revised for the current study. The revision, which aimed to provide a balanced MEP with specific, adequate, and intensity-demanding tasks, comprises adjustments of contents (motor qualities as well as connection between motor and cognitive tasks) and intervention duration (extension to 16 weeks).

The MEP will be guided by 2 skilled instructors with experience in sports science and performed as group training mainly in a seated position. A group will consist of a maximum of 12 participants and will be joined by familiar caregivers to support the instructors if needed. The underlying didactic concept focuses on specific needs and characteristics of IWD and includes increased supervision realized by 2 instructors, adaptation to the cognitive level of participants, adjusted communication (eg, simple language, nonverbal aspects), ritualization to give orientation and familiarity, and adequate complexity by simple and well-structured cognitive and motor tasks.

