### Dropout

We assume 3 reasons for dropout: (1) withdrawal from the study, (2) missing data, and (3) low attendance or adherence to MEP. Possible reasons for withdrawal are death, hospitalization, serious deterioration in state of health, refusal to participate, etc. Based on the literature review of Blankevoort et al [22], a dropout rate of 20% caused by withdrawal is expected. Missing data occur if participants are not able to complete the entire test battery because of motivational aspects or multiple motor and cognitive impairments. In addition, some participants will not participate at all in postassessments because of illness or other appointments. We assume a missing data rate of 15%. A total target number of 200 participants (100 per group) for the analysis and an assumed dropout rate (withdrawal and missing data) of 35% requires enrolling 270 participants into the study. Unfortunately, attendance and adherence are often not stated in previous studies [26]. Hence, we decided to double the sample of IG to ensure the required sample of 100 participants in this group. Low attendance and adherence may be caused by illness, motivation, other appointments, disinterest, or other reasons. Hence, a total sample size of 405 participants is required.

All participants will be asked at least twice if they are willing to participate in the assessments to reduce missing data. A familiar caregiver is asked to invite the participant if appropriate. If participants are not willing to complete all measures they are offered to choose assessments they are willing to complete. Moreover, all possible participants will be included in the data collection regardless of whether they discontinued or deviate from the intervention protocol. Caregivers will be asked to support the participants to get to training sessions to improve attendance. If participants miss a session, they are personally invited to the next training session.

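### As written, one 70% probability for the better fitting group, with minimization restarted in each care facility, does not deliver the stated 2:1 allocation

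*Protocol article*

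**What the plan says.** The Study Design section sets "an allocation ratio of 2:1 for intervention (IG) and control group (CG), respectively". The Dropout section gives the reason. Attendance and adherence are poorly documented in earlier studies, so "we decided to double the sample of IG to ensure the required sample of 100 participants in this group", and this brings the total to 405. The Allocation section repeats the ratio: "An allocation ratio of 2:1 is selected because of above-mentioned assumptions regarding dropouts".

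The same section then fixes the mechanism:

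- The unit is the facility: "minimization will be done separately for each care facility".
- The factors are four: "based on the baseline criteria MMSE, sex, age, and baseline performance of modified 30-second chair-stand test".
- The start is a chance draw: "The first participant is allocated randomly to IG or CG".
- After that, "participants will be allocated to the better fitting group with a probability of 70" percent.

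The article gives one probability, does not say that it differs by arm, and names no other device for reaching 2:1.

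**The concern.** A biased coin with the same probability for either arm suits a 1:1 target. Under 2:1 it is lopsided. When IG is behind, its chance of 0.70 barely exceeds the 0.667 that it needs just to keep pace, so a deficit is hardly repaired. When CG is behind, it gets 0.70 against a target of 0.333, so an IG surplus is cut back sharply. Each facility starts again from zero, so the sequences are short and the early IG deficit recurs in each one.

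At stake are the planned 270 and 135, and in particular the extra IG participants meant to protect the per-protocol set defined under Statistical Analysis, which requires sufficient attendance and adherence.

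**Working it through.** **The plan's own figures.** The Dropout section inflates 200 by 35%: 200 × 1.35 = 270, or 135 per group. Doubling IG gives 270 + 135 = 405. The total reproduces, and 2:1 is built into it.

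**Inputs from the article.** Target IG share 2/3; probability 0.70 for the better fitting group; restart in each facility; four factors; total 405.

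**Assumptions, because the article gives no value.** Participants per facility, 6 to 60 (a training group holds at most 12, so one full IG group at 2:1 implies 12 + 6 = 18); two or three levels per factor; first participant and ties at 1/2 or 2/3; group counts compared after scaling to 2:1.

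**Step 1: share of draws needed.** Let q be the share of draws on which IG fits better. Then 0.70q + 0.30(1 − q) = 2/3, so q = (0.6667 − 0.30) / 0.40 = 0.917. This needs no assumption about facility size.

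**Step 2: direction of pull.** Let D = n_IG − 2·n_CG, which is zero at exactly 2:1. The expected change in D per participant is:

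- IG preferred: 0.7 − 2(0.3) = +0.1
- CG preferred: 0.3 − 2(0.7) = −1.1

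**Step 3: size.** The four-factor simulation restarts in each facility. The last column is an exact recursion on D alone, ignoring the factors.

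| Participants per facility | IG share | IG:CG | IG of 405 | IG:CG, size only |
|---|---|---|---|---|
| 9 | 0.597–0.611 | 1.48–1.57 | 242–247 | 1.41–1.49 |
| 12 | 0.601–0.615 | 1.50–1.60 | 243–249 | 1.46–1.53 |
| 18 | 0.604–0.616 | 1.53–1.60 | 245–249 | 1.54–1.60 |
| 24 | 0.613–0.619 | 1.58–1.63 | 248–251 | 1.60–1.64 |
| 36 | 0.615–0.625 | 1.60–1.66 | 249–253 | 1.67–1.70 |
| 60 | 0.625–0.635 | 1.67–1.74 | 253–257 | 1.75–1.77 |
| one run of 405 | 0.655–0.656 | 1.90–1.91 | 265–266 | 1.94 |

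Repeat runs put the range for 9 to 24 at 0.595 to 0.62: 405 × 0.595 = 241 and 405 × 0.62 = 251 IG, leaving 164 and 154 CG.

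**Step 4: consequence.** Apply the article's 35% loss and ask what fraction of the remaining IG could adhere poorly before fewer than 100 are left.

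- Planned: 270 × 0.65 = 175.5; 1 − 100/175.5 = 43%.
- 251 IG: 163.2; 1 − 100/163.2 = 39%.
- 241 IG: 156.7; 1 − 100/156.7 = 36%.

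For the all-randomized comparison, the effective sample size 4·n_IG·n_CG/N is 4 × 270 × 135/405 = 360 as planned. It becomes 4 × 251 × 154/405 = 382 or 4 × 241 × 164/405 = 390. It rises.

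**Step 5: does a change of probability cure it?** If IG is preferred on two thirds of draws, both example pairs average exactly 2/3:

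- 0.80 (IG preferred) and 0.60 (CG preferred): (2/3)(0.80) + (1/3)(0.40) = 0.667; simulated 0.652–0.668 at 9 to 60 per facility.
- 0.85 and 0.70: (2/3)(0.85) + (1/3)(0.30) = 0.667; simulated 0.656–0.674.

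**The case against.** The strongest reply is that the outcome depends on a software setting that the article does not show. The minimization program may treat 70% as a base value and raise it for IG once 2:1 is selected; the split would then be close to 2:1. That stands as a possibility. It does not remove the point, because the article states the number and gives no second one. In that case the procedure is sound and the description is incomplete. For the same reason, a reader might infer that the trial was in fact randomized at about 1.5:1. The documents do not show this; the finding concerns the rule as described.

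The size also rests on an unstated facility size. Over 6 to 60 per facility and both models, the range is about 1.3 to 1.8:1. The shortfall shrinks as facilities grow, so the 70% alone does not make 2:1 unreachable. The fault is that probability combined with short sequences.

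A reader might further infer lost power or bias. Neither follows. Effective sample size rises, and CG moves toward its required 100: after 35% loss, 135 leaves 88, whereas 154 to 164 leaves 100 to 107. Nothing in the rule favours one arm prognostically. The article states no expected adherence rate, so the smaller IG reserve cannot be called inadequate either.

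Finally, 1:1 would be expected if the program compared unscaled counts. Since the article says that 2:1 is selected, scaled counts are the fairer reading.

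**Conclusion.** The point holds in a limited form: the Allocation section states a ratio that its stated rule does not have. The 92% requirement and the +0.1 against −1.1 pull follow from the text alone. The expected split of about 1.5 to 1.6:1 is conditional on 9 to 24 participants per facility and on the assumptions about factor levels, ties and the first draw. At those sizes, IG falls short of 270 by about 19 to 29 participants, and the low adherence that it can absorb drops from 43% to between 36% and 39%. The harm is confined to that reserve and to the stated arm sizes. It is worth correcting, but it does not threaten the validity or power of the main comparison.

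**What to change.** First establish from the allocation records which probability the program applied to each arm. Then:

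- **If it already adjusted for 2:1:** correct the Allocation section to give the probability used when IG is preferred and when CG is preferred.
- **If 0.70 was used for both, in facilities not yet allocated:** set and state arm-specific probabilities consistent with 2:1. The pairs 0.80/0.60 and 0.85/0.70 are examples; each gives an IG share of about 0.66.
- **If 0.70 was used for both, in facilities already allocated:** leave the allocations as they are, and restate the expected ratio and arm sizes.

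The cost is a program setting and a sentence or two. IG draws become somewhat more predictable when IG is preferred, but the input order is already random. Enrolment began in May 2015, so a change would leave two rules in use across facilities; report which facilities used which. If few facilities remain, the correction is one of reporting only.

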### Blinding and Pseudonymization

Investigators will be blinded to allocation wherever possible. It is not possible to blind participants or employees of care facilities regarding group allocation.

All data is stored in a strictly pseudonymous form. This is achieved by separating personally identifiable information of participants from data collected during baseline and postassessments. Collation of data is only possible with considerable effort at any time of the study. Thus, individual confidentiality will be ensured before, during, and after the study. Only selected team members have access to coded data.

### Statistical Analysis

All statistical analysis will be done with SPSS version 23 (IBM Corp). Trained and experienced investigators will evaluate and enter data. Investigators evaluating and entering data are not the same as investigators assessing outcomes. The number of investigators is limited to 2 per assessment method. Prior to actual analysis, interrater reliability (Cohen kappa [76], intraclass correlation coefficient [77]) will be calculated and plausibility (eg, considering range and distribution) will be checked to minimize errors caused by data evaluation and entry.

Because of expected large dropout rate, which can lead to a critical amount of missing data, 2 separate analysis sets are planned: an intention-to-treat analysis and a per-protocol analysis. In the intention-to-treat analysis, all randomized participants regardless of protocol adherence will be included and missing data will be substituted by multiple imputation. Participants with sufficient attendance and adherence to the intervention as well as complete assessments of primary outcomes will be included in the per-protocol analysis, where missing data will not be considered.

Baseline values of participant characteristics will be compared between IG and CG using chi-square tests for categorical data, Mann-Whitney-U tests for nonparametric variables, and *t* tests for continuous and normally distributed parameters. For all normally distributed data (checked by Shapiro-Wilk test), mean and standard deviation will be calculated, and medians and interpercentile ranges will be calculated for not normally distributed data. Treatment effects will be analyzed using 2-factor ANOVA with repeated measurement. A 2-sided *P* value less or equal to .05 will be considered to indicate statistical significance. In addition, 95% confidence intervals and partial Eta² will be calculated. Changes in motor and cognitive function are possible mediators and moderators. These mediating and moderating effects on primary outcomes will be analyzed using multiple linear regression models. Additional explorative data analysis exceeding the proposed planned analyses will be performed. Depending on data structure, adequate analysis methods will be defined. These analyses aim to consider further influencing factors or subgroup analysis as well as the development of forecast models.

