### Participants

Participants for this study will be recruited in public, private, and charitable care facilities in southwestern Germany, in particular in the metropolitan region Rhein-Neckar and the district around Karlsruhe. All randomly selected care facilities offer inpatient care for approximately 60 to 300 residents and provide a common room where the intervention will be performed. A total of 3 recruitment periods with consecutive sampling within each care facility are planned.

Employees of care facilities will identify possible participants with the purpose to fulfill selection criteria.

Inclusion criteria include (1) diagnosis of dementia or suspected dementia (based on the assessment of the objective ICD-10 criteria by employees and the examination of cognitive abilities with Mini-Mental State Examination [MMSE][45]), (2) Alzheimer disease, vascular dementia, or other primary dementia (all types caused by neurodegenerative or vascular diseases: eg, lewy body dementia or frontotemporal dementia [46]), (3) mild to moderate stage of dementia (MMSE 10-24), (4) age above 65 years, (5) walking ability of approximately 10 meters with or without walking aid, and (6) clearance by general practitioner.

Exclusion criteria include (1) secondary dementia (all types resulting from organic illness or injury: eg, toxic substances or brain injuries [46]), (2) other severe cognitive impairments, (3) other severe neurological disease, (4) other severely acute diseases, and (5) severe motor impairments.

Potential participants will receive a comprehensive information letter and an informed consent form, which will be signed by individuals or their legal guardians prior to the study. The informed consent along with clearance of participant’s general practitioner allow scheduling of baseline assessments where eligibility will be verified according to the inclusion and exclusion criteria. Flow of participants is illustrated in Figure 1.

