**Primary outcomes**		
	Balance	Frailty and Injuries: Cooperative Studies of Intervention Techniques 4 (FICSIT-4) [51]
	Mobility	
		Timed Up and Go test [52]
		6-meter walk test [53]
	Gait	Gait analysis using GAITRite: temporal and spatial gait parameters (gait speed, cadence, cycle time, step length, step width, gait variability, single support, and double support)
		- Walking with normal speed
		- Walking with normal speed and the task counting backwards from 50
		- Walking with normal speed and the task naming animals

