#### Primary Outcomes

Static balance will be determined using the Frailty and Injuries: Cooperative Studies of Intervention Techniques 4 scale (FICSIT-4) [51]. Mobility will be assessed using the timed Up and Go test [52] and 6-meter walk test [53]. The 6-meter walk test aims to capture normal gait speed. To reduce bias caused by the testing situation, participants are not explicitly informed about time keeping.

Temporal and spatial gait parameters will be analyzed using the electronic gait analysis system GAITRite (CIR Systems Inc, Franklin, NJ) with an active length of 4.88 meters, a spatial resolution of 1.27 centimeters, and a scan rate of 120 hertz. The following parameters are of special interest: gait speed, cadence, cycle time, step length, step width, gait variability, single support, and double support (as percentage of cycle time). Gait parameters are recorded for 3 different conditions: walking with normal speed, walking with normal speed and the task of counting backwards from 50, and walking with normal speed and the task of naming animals.

Changes in gait parameters caused by dual task will be calculated using the equation seen in Figure 3. The generated value represents dual-task costs indicating the better performance under dual-task condition the lower this value is [66,67].

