### Challenges

There are several challenges in performing intervention studies in IWD. These are related to the selected study design as well as its target group and thus cannot be avoided. However, it is important to deal with these challenges to minimize their impact.

A big challenge in performing intervention studies with IWD is maintaining blinding to group allocation. Although all investigators will be blinded to group allocation, there is a potential risk that participants will disclose their group allocation during assessments. To minimize this risk, investigators will be asked not to talk about the intervention during assessments.

Working with IWD entails several general challenges as they are often suffering from frailty and multimorbidity. According to different motor and cognitive impairments in IWD, it is not possible to develop an intervention completely suitable for all participants. Hence, some adaptions of the intervention cannot be avoided. However, instructors are asked to minimize such adaptions and adhere to the manual as strictly as possible. Besides this, IWD are vulnerable in relation to attendance, adherence, and missing data. For instance, multiple motor and cognitive impairments partially prevent IWD from participating in all subassessments. Thus, attempts to enhance attendance and adherence as personal communication, support, or repeated invitation are planned.

Further challenges are seen in cooperation with care facilities. Employees assume important responsibilities, such as suggesting potential participants, assessing ADL and state of health, or supporting assessments and intervention. Restricted time or missing expertise is a potential risk for limitations. To reduce such limitations, employees will be provided detailed information on how to report required data and support for further problems.

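### Requiring every primary outcome to be complete for per-protocol entry discards valid balance and mobility data and is likely to under-represent the more impaired participants

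*Protocol article*

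**What the plan says.** The Statistical Analysis section plans two sets. In the intention-to-treat set, "all randomized participants regardless of protocol adherence will be included and missing data will be substituted by multiple imputation". For the other set, "Participants with sufficient attendance and adherence to the intervention as well as complete assessments of primary outcomes will be included in the per-protocol analysis". Gaps are not filled in for this second set, which is described as one "where missing data will not be considered". Neither set is named as the primary one.

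Table 2 and the Primary Outcomes section list what has to be complete: FICSIT-4 for balance, Timed Up and Go and the 6-meter walk for mobility, and GAITRite gait analysis in three conditions. The conditions are walking at normal speed, "walking with normal speed and the task of counting backwards from 50, and walking with normal speed and the task of naming animals".

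The Participants section admits MMSE scores from 10 to 24. The Dropout section attributes missing data partly to motor and cognitive impairment, assumes a rate of 15%, and offers participants who decline the full battery a choice of tests. The Challenges section repeats that "multiple motor and cognitive impairments partially prevent IWD from participating in all subassessments".

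**The concern.** A per-protocol set is meant to hold those who followed the protocol. Here entry also depends on finishing every primary test, and the article says that ability affects whether tests are finished. A fully adherent participant with valid balance, Timed Up and Go and 6-meter walk results at both visits is lost from the balance analysis because one dual-task walk is missing. A missing walk says nothing about whether that person's balance data are valid or whether the programme was followed.

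Two things are at stake. Valid data on two of the three primary domains are discarded in that set. The set is also selected on ability, so its result may describe a less impaired group than the one enrolled.

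In the control group the effect is starker. Controls are not in the exercise programme, so attendance and adherence cannot screen them, and test completeness is the only stated criterion that can exclude them.

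**Working it through.** **1. The plan's own figures.** The Dropout section adds 20% withdrawal and 15% missing data to get 35%.
- 200 × 1.35 = 270, which is 135 per group.
- Doubling the intervention group gives 270 + 135 = 405. Both totals reproduce.
- The 200 itself reproduces with f = 0.10 and an assumed pre-post correlation of 0.5, which the article does not state (power 0.804).

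Missing data and low attendance or adherence are both counted as dropout on the way to 100 per group. The sample size is therefore aimed at something close to the per-protocol set, so that set is not a side issue.

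**2. A ceiling on the loss from this rule.** The 15% covers failure to complete the whole battery, secondary tests included, and also people who miss postassessment altogether. Those absent at post would be lost under any rule that requires post values. The loss specific to this rule is therefore below 15%. Of 405 enrolled that is fewer than 0.15 × 405 ≈ 61 people (about 41 of 270 intervention and 20 of 135 control). The 15% is the plan's assumption, not an observed rate.

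**3. Worst case for moderate-stage participants.** Let s be the moderate share of the sample (not in the article), and place all of the 15% on that stage. The share of them retained is max(0, s − 0.15)/s.

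| s | retained |
|---|---|
| 0.30 | 0.15/0.30 = 50% |
| 0.50 | 0.35/0.50 = 70% |
| 0.70 | 0.55/0.70 = 79% |

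Complete removal would need s ≤ 0.15.

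**4. Illustrative shift in stage mix.** Assume half the sample is mild, with probability a (mild) and b (moderate) of missing at least one dual-task walk. None of these values is in the article. Kept = 0.5(1−a) + 0.5(1−b). Mild share afterwards = 0.5(1−a)/kept.

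| a | b | kept | mild share |
|---|---|---|---|
| 0.05 | 0.20 | 87.5% | 54% |
| 0.05 | 0.30 | 82.5% | 58% |
| 0.10 | 0.40 | 75.0% | 60% |

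Only the first row, a loss of 12.5%, lies under the 15% ceiling. The other two suppose more missing data than the plan does.

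**5. Sensitivity to joint completeness.** Take six test blocks, each 95% complete. If failures were independent, 0.95^6 = 73.5% would be complete at one visit and 0.95^12 = 54.0% at both. If the same people failed everything, 95% would be complete. Failures driven by impairment cluster in the same people, so the truth lies above 54%, and that figure should not be used as an estimate. Under independence, staying within 15% would need 0.85^(1/12) = 98.7% completion per block per visit.

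**The case against.** A reader might infer that the rule removes the moderate-stage participants whom the MMSE 10-24 criterion was written to include. The article does not support this. It gives no completion by MMSE stage and no moderate share, and it nowhere says that these participants cannot do the dual-task walks. The Challenges section speaks of impairment in general and says only that it partially prevents testing. Even the illustrative failure rates above keep 60-80% of the moderate stage.

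Other counter-arguments carry weight:

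- The intention-to-treat set keeps every randomised participant and uses their partial data. This limits the damage to one of two sets, although the article does not say which set leads.
- Poor counting or naming is not a missing walk. The Primary Outcomes section sets no minimum performance on the secondary task. The Determination of Outcomes section also reports that a 20-person pilot proved the battery feasible. However, it gives no completion rates, and the Dropout and Challenges sections still expect incomplete testing.
- Completeness might have been meant outcome by outcome, with the detail in a fuller plan. That is possible. But the sentence states one set with one entry rule and refers to the primary outcomes jointly. If the other meaning was intended, the sentence needs to say so.
- Attendance and adherence select on health too. The Dropout section lists illness and motivation as causes, and the Intervention section rates adherence on attention, participation, motivation and behavior. Dropping the completeness rule would therefore not turn the contrast between the two sets into a clean effect of adherence. This stands in full.

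**Conclusion.** The point holds as a fault in a stated rule. Followed as written, the rule excludes adherent participants with valid balance or mobility data because an unrelated test is missing. It also ties entry to ability, through a link that the article itself makes. Under-representation of the more impaired part of the MMSE 10-24 range in the per-protocol set is likely.

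Its size cannot be established from the article. If the planned 15% is right, the loss specific to this rule is below that. With an assumed even split of stages, at least 70% of the moderate stage stays in. A shift in the mild share from 50% to about 54% is an illustration on assumed failure rates, not an estimate. The discarding of valid data does not depend on any assumed stage split.

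**What to change.** Change the sentence that defines the per-protocol set:

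- Membership rests on eligibility, attendance and adherence.
- Each primary outcome is analysed in all members who have baseline and post values of that outcome, with each GAITRite condition counted separately.
- The MMSE distribution of each outcome's set is reported, by arm, beside that of the intention-to-treat set.

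No data collection changes. The cost is that the number analysed differs between outcomes and must be stated for each. The change recovers usable data and reduces selection on ability, but does not end it: people who cannot do a dual-task walk will still be absent from that walk's analysis. The report should also say that differences between the two sets cannot be read purely as an effect of adherence.
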